## Abstract

**Background:**

Decline of renal function is common in older persons and the prevalence of chronic kidney disease (CKD) is rising with ageing. CKD affects different outcomes relevant to older persons, additionally to morbidity and mortality which makes CKD a relevant health burden in this population. Still, accurate laboratory measurement of kidney function is under debate, since current creatinine-based equations have a certain degree of inaccuracy when used in the older population. The aims of the study are as follows: to assess kidney function in a cohort of 75+ older persons using existing methodologies for CKD screening; to investigate existing and innovative biomarkers of CKD in this cohort, and to align laboratory and biomarker results with medical and functional data obtained from this cohort. The study was registered at ClinicalTrials.gov, identifier NCT02691546, February 25th 2016.

**Methods/design:**

An observational, multinational, multicenter, prospective cohort study in community dwelling persons aged 75 years and over, visiting the outpatient clinics of participating institutions. The study will enroll 2450 participants and is carried out in Austria, Germany, Israel, Italy, the Netherlands, Poland and Spain. Participants will undergo clinical and laboratory evaluations at baseline and after 12 and 24 months- follow-up. Clinical evaluation also includes a comprehensive geriatric assessment (CGA). Local laboratory will be used for ‘basic’ parameters (including serum creatinine and albumin-to-creatinine ratio), whereas biomarker assessment will be conducted centrally. An intermediate telephone follow-up will be carried out at 6 and 18 months.

**Discussion:**

Combining the use of CGA and the investigation of novel and existing independent biomarkers within the SCOPE study will help to provide evidence in the development of European guidelines and recommendations in the screening and management of CKD in older people.

**Trial registration:**

This study was registered prospectively on the 25th February 2016 at clinicaltrials.gov (NCT02691546).

## Background

Evidence from epidemiological and clinical literature suggests that ageing contributes to the incidence of reduced renal filtration capacity [1]. In the presence of risk factors during ageing, such as diabetes, hypertension and others, filtration capacity further declines. This concept is underlined by many epidemiological studies showing a decline of measured estimated glomerular filtration rate (eGFR) with advancing age [2]. Kidney function is usually assessed by creatinine-based estimated glomerular filtration rate (eGFR) equations. However, those formulae have a certain degree of inaccuracy when used in older people due to changes in anthropometry and renal physiology during ageing [3]. Alternative filtration markers yielded different eGFR values for different cohorts of people tested [4]. This inaccuracy of laboratory measurements of kidney function suggests a risk of underdetection or overdetection of CKD, especially with advancing age [5]. Indeed, the eGFR threshold at which the risk of negative outcomes increases among older patients is hotly debated [6], and current evidence suggests that such a threshold may be lower among older people compared to adult ones [7–9]. Additionally, the eGFR cut-offs at which the risk of death starts to increase may change as a function of the equation used among older people [10]. Thus, improving accuracy of CKD screening measures for older populations would be of help in reducing the risk of underdiagnosis to maximize prevention of CKD and its consequences while minimising the risks and cost of overdiagnosis [6].

Diminished kidney function has become a relevant public health burden for all age groups, as CKD frequently results in an increased risk of end stage renal disease (ESRD), morbidity and mortality [11]. Besides “traditional” endpoints, CKD has been shown to impact nutritional status, inflammatory processes and anemia [12], thereby affecting different outcomes especially relevant to older people. These include impaired physical function, frailty and disability [13–16], cognitive impairment and dementia [17–19], depression [20–22], sensory impairment [23], undernutrition and sarcopenia [24–26], and adverse drug reactions (ADRs) [27, 28]. Therefore, early and sensitive detection of diminished renal function is essential to individually address care needs of older people with CKD and to address one of the major health burden in public health for the incoming decades [29].

Incorporating scoring risk models for care planning of older people at risk for CKD has come into focus recently [30]. Risk prediction models are generally based on equations designed on the basis of prognostic factors and clinical outcomes, available at the time the prediction is made, and collected in specific and representative cohorts of individuals followed up for a given period of time [31]. Built on evidence of such models, screening programmes for CKD can take into account the characteristics of the target population in addition to simple laboratory measures, biomarkers and disease-based investigations. Multi- and co-morbidity, polypharmacy, frailty, functional and cognitive impairment and disability should be considered as part of a patient centered approach in CKD management especially in older adults [15, 23–26, 32–35].

So far, no CKD screening program has included all those variables also including data from comprehensive geriatric assessment (CGA), the only assessment technology able to capture the numerous domains of health status and their complex interactions in older people. Accordingly, the need for laboratory measurements able to identify accurately older people with CKD is a demand to address the public health challenges arising from the current demographic shifts. Indeed, this view is widely shared by the geriatric and nephrology communities, both in EU and USA [36, 37].

The aims of this multicenter study in Europe are to assess existing methodologies for CKD screening and investigate existing and innovative biomarkers of CKD in older persons. Furthermore, the Screening for CKD among Older People across Europe (SCOPE) study will provide evidence for including physical and functional health parameters of older people across Europe and help design a tailored risk prediction model for CKD in old age.

## Methods

### Study design

The SCOPE study is designed as an observational, multinational, multicenter, prospective cohort study in persons older than 75 years across Europe. This study is carried out in seven countries, including Austria, Germany, Israel, Italy, the Netherlands, Poland and Spain. Participants will undergo clinical and laboratory evaluations at the baseline (recruitment), and will be followed up at face to face visits at months 12 and 24 following enrollment. An intermediate telephone follow-up will be carried out at 6 and 18 months following recruitment. Figure 1 shows the schematic flow of the observational clinical study.

**Fig. 1 Fig1:**
[figure not shown]
Study design of the SCOPE project

The study design complies with the Declaration of Helsinki and Good Clinical Practice Guidelines. The enrollment has started in August 2016 and is ongoing.

### Ethical approval/ monitoring

The study protocol was approved by ethics committees at all participating institutions. Patients are requested to sign a written informed consent before entering the study. Patients are also asked to sign a separate informed consent to the collection of DNA samples to be used for genetic testing, while those not giving their consent will be retained in the main cohort study.

In order to ensure high ethical and scientific standards of the project and to monitor the progress of the clinical study a Scientific Advisory Board (SAB) and a Data and Ethics Management Board (DEMB) was implemented within the Governance Structure. The SAB ensures a high standard of research, monitors the progress of the project by taking part in the project meetings, and provides final approval to any required study amendments. The DEMB supports the preparation of the relevant end-points for ethical review, advises on local research Ethical Committee applications, and reviews the relevant safety, morbidity and mortality end-points during the course of the study. The DEMB maintains an overview of the work throughout the whole course of the project and helps to foresee possible problems that might arise and how they can be addressed.

### Study population

Persons aged 75 years and older, visiting the outpatient clinics of participating institutions are eligible for inclusion. The study design aims at minimizing self-selection bias and enrolling real-world patients without stringent inclusion/exclusion criteria. The few exclusion criteria are outlined in Table 1. Therefore, no other inclusion criteria will be considered. The SCOPE study aims to finally enroll 2450 participants.

**Table 1 Tab1:** Exclusion criteria for participants enrollment into the SCOPE project

• Age < 75 years	
• End stage renal disease (< 15 mL/min/1.73 m2) or dialysis at time of enrollment	
• History of solid organ or bone marrow transplantation	
• Active malignancy within 24 months prior to screening or metastatic cancer	
• Life expectancy less than 6 months	
• Severe cognitive impairment (Mini Mental State Examination < 10)	
• Any medical or other reason (e.g. known or suspected inability of the patient to comply with the protocol procedure) in the judgement of the investigators, that the patient is unsuitable for the study	
• Unwilling to provide consent and those who cannot be followed-up	

### Study visits

Following enrollment, participants will be seen by the study teams at 12 and 24 months at a face to face meeting. Demographic data and socioeconomic status (occupation before retiring, economic status, formal and informal care) will be documented and followed up at each visit. Physical examination will be performed by medical doctors due to standardized procedure given in the visit protocol. Medical history and use of medication and adverse drug reactions classified according to the World Health Organization (WHO) definition [38] will be collected during follow-up visits. During all face to face visits a comprehensive geriatric assessment (CGA) will be performed. Table 2 shows all domains checked during study visits [39–51] [52].

**Table 2 Tab2:** Comprehensive Geriatric Assessment domains tested during the SCOPE project

• Basic (ADL) and Instrumental Activities of Daily Living (IADL)/self-reported disability [39, 40]	
• Mini Mental State Examination (MMSE)/cognitive status [41]	
• 15-items Geriatric Depression Scale (GDS)/mood [42]	
• Cumulative Illness Rating Scale (CIRS)/overall comorbidity [43]	
• History of falls and incident falls	
• Vision and hearing impairment will be coded on a scale from 0 (adequate) to 4 (no vision/hearing present) [44].	
• Lower urinary tract symptoms (LUTS): The presence of LUTS will be ascertained by asking the patient to rate on a 5-point (0–4) Likert scale how big a problem, if any, has each of the following items been during the last 4 weeks: 1. Dripping or leaking urine, 2. Pain or burning in urination, 3. Bleeding with urination, 4. Weak urine stream or incomplete emptying, 5. Waking up to urinate, 6. Need to urinate frequently during the day [45].	
• Nutritional status: anthropometric parameters (calf circumference, arm circumference, Body mass index (kg/m2), waist-hip ratio, waist-to-height ratio), Mini Nutritional Assessment (MNA) [46] and 24-h dietary recall^a^ [47].	
• Short Physical Performance Battery (SPPB) [48].	
• Grip strength [49] measured by using JAMAR hydraulic dynamometer.	
• Bioelectrical impedance analysis (BIA)^b^ [50] Muscle mass will be calculated using the Janssen et al. equation [51], using the instrument Akern BIA101.	
• Health related quality of life will be rated by the Euro-QoL 5D.	

^a^Data obtained from the 24-h dietary recall will be analyzed using nutritional databases suitable for the patient’s country. Following the analysis, a detailed report (containing levels of consumption of various nutrients and energy) will be available. This level will be compared with recommended levels of intake

^b^BIA will not be performed in patients with pacemaker or implantable cardioverter defibrillator

Healthcare resource consumption will be evaluated using a resource use questionnaire within a 6-month recall time-frame [50]. Following information will be retrieved: previous physician visits (GPs, specialists, or physician at the Emergency Room), use of diagnostic tests and specialist clinic procedures, use of care services (e.g. Nurse home visit, Physiotherapy, Home help, Social transport, Day care center) and hospital admissions (number and duration of hospitalization, type of reimbursement).

Furthermore, caregiver burden will be measured using the Zarit Burden Interview (ZBI) [53].

During enrollment and at the two face to face follow up visits blood and urine samples will be collected and analysed for serum creatinine, urinary albumin and albumin-to-creatinine ratio.

### Telephone follow-up

At 6- and 18-month participants and/or caregivers will be interviewed by phone to collect information on vital and functional status and healthcare resource consumption. Changes in medical history and adverse drug reactions will also be collected.

### Laboratory parameters and biomarkers

Serum creatinine measurement will be standardised to Isotope-Dilution Mass Spectrometry at local level, when the method is available. Creatinine-based eGFR will be calculated using the Berlin Initiative Study 1 (BIS1) equation, which is the only method specifically developed in a population older than 70 years [54]. ESRD will be defined as GFR < 15 mL/min/1.73 m2 or dialysis [55]. In case of unavailability of standardized creatinine methodology at local level, this measurement will be made by INRCA laboratories afterwards. The panel of laboratory parameters to be measured at baseline, 12-month and 24 months by local laboratories will also include: complete blood cells count, lipids profile, electrolytes, nutritional status, and urine analysis.

The project will also include the collection of blood and urine samples to investigate existing and innovative biomarkers of kidney function. Existing biomarkers of CKD like Cystatin C (CysC) [56], β-Trace protein (BTP), also known as lipocalin prostaglandin D2 synthase [57, 58] Beta2-microglobulin [59] will be measured using published and established methods. Potential and new biomarkers will be also evaluated. Furthermore, the evaluation of experimental kidney damage biomarkers as well as untargeted analysis of metabolomics in serum and urine is currently be performed in ULSAM [60] and PIVUS [61] studies, in order to identify additional kidney damage biomarkers that may be validated in the SCOPE project. Table 3 shows an overview on current, alternative and innovative biomarkers for CKD whose applicability in old age will be investigated within the SCOPE project.

**Table 3 Tab3:** Biomarkers research in the SCOPE project

Current screening methods^a^	Alternative screening methods^b^	Innovative screening methods^b^
Serum creatinine	Serum cystatin C	Serum fibroblast growth factor 23
Creatinine-based eGFR	Serum β-trace protein	Serum and urinary soluble TNF receptor 1
Urinary albumin	Serum β2-microglobulin	Seerum and urinary soluble TNF receptor 2
Albumin-to-creatinine ratio		Serum and urinary osteopontin
		Serum penthraxin 3
		Serum and urinary endostatin
		Serum and urinary TIM-1 (KIM-1)
		Serum TRAIL R2
		Serum and urinary endostatin

^a^current screening measures will be assessed at local laboratories and are immediately available after enrollment and follow-up visits;

^b^alternative and innovative screening measures will be centrally assessed and will be concealed until data analysis

The assessment of selected genetic and epigenetic parameters involved in hallmarks of aging will be also carried out to investigate their relationship with kidney function. This latter assessment will be limited to participants who signed a separate informed consent (patients not giving informed consent for genetic and epigenetic analysis will be retained in the main cohort study), and will include: DNA methylation, polymorphisms of mitochondrial DNA, polymorphisms of genes coding for pro- and anti-inflammatory cytokines (IL-6, IL-1, TNF-alpha, IL-10, IL-2, IL-17, IL-8) and chemokines (MCP-1 and RANTES), polymorphisms associated with molecules involved in the pathogenesis of metabolic and neurodegenerative diseases such as insulin and IGF-1 signaling pathway and APOE, Klotho, mTOR, and whole genome analysis by Affymetrix Chip Array 6.0.

### Measured glomerular filtration rate

The assessment of measured glomerular filtration rate (mGFR) will be performed by single-dose inulin clearance [62, 63]. Participants will be asked to sign a separate informed consent to participate in this sub-study, while those not giving their consent will be retained in the main cohort study. The objective of this sub-study will be the derivation of new eGFR equation(s) based on already known and/or novel biomarkers. The accuracy of new equation(s) in predicting mGFR will represent the primary study endpoint. Accuracy will be assessed by P30 (percentage of estimates within 30% of the mGFR). A sample of 400 participants will enable us to detect a difference of 2% in P30 between the new equations (based on the innovative and novel biomarkers) and the BIS equations, with significance level 0.05 and power 0.8 (considering a 1-sample and 1-sided test). In addition, we have evaluated that the sample will be sufficient to detect a statistically significant difference in 4,3 points in the Area under the ROC curve using the new equation(s) for discriminating participants below the critical threshold of 60 ml/min/1.73 m^2^. Finally, the availability of mGFR in a subgroup of participants enrolled in the study will be used to investigate the relationship between innovative biomarkers and objectively measured kidney function.

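### The claim that 400 sub-study participants detect a 2-point P30 difference holds only if BIS P30 is about 95–97%, which is not stated, and it treats BIS P30 as a known constant

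*Protocol article*

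**What the plan says.** The section Measured glomerular filtration rate of the protocol article describes a consent-based sub-study with single-dose inulin clearance, meant to derive new eGFR equations. Accuracy in predicting mGFR is its primary endpoint: "Accuracy will be assessed by P30 (percentage of estimates within 30% of the mGFR"). The sample-size statement reads: "A sample of 400 participants will enable us to detect a difference of 2% in P30 between the new equations". The comparator is BIS, and the calculation takes alpha as 0.05 and power as 0.8, in the form described by the words "considering a 1-sample and 1-sided test".

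The article gives no assumed P30 for BIS and no assumed agreement between the equations. Two other statements bear on the design. The same section refers to "the availability of mGFR in a subgroup of participants enrolled in the study", so an in-study P30 can be computed only there. Laboratory parameters and biomarkers plans BIS1 eGFR from the study's serum creatinine.

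**The concern.** The sample size of a one-sample test of a proportion depends strongly on the reference proportion. A 2-point gain is easy to see when the reference is close to 100% and hard to see elsewhere. The article states the sample size, the difference, alpha, power and the type of test, but not the reference P30 that decides whether they fit together.

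The calculation also takes BIS P30 as fixed. If BIS is scored on the sub-study participants, its P30 is an estimate with sampling error and is paired with that of the new equation. Power then depends on the share of people for whom only one of the two equations falls within 30% of mGFR.

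At stake is the reading of the sub-study's primary endpoint. If the sub-study has much less than 80% power for the gain it names, a non-significant result could be taken to show that the new equations bring no improvement over BIS.

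**Working it through.** **Inputs from the article:** n = 400; difference d = 0.02 (2% read as 2 percentage points); one-sided alpha 0.05 (z = 1.645); power 0.80 (z = 0.842). **Not given, so assumed over a range:** the BIS P30 (p0) and the discordant share (ψ).

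**Step 1. Reproduce the 400.** The one-sample score form, with p1 = p0 + 0.02, is

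n = [(1.645·√(p0(1−p0)) + 0.842·√(p1(1−p1))) / 0.02]²

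Solving for n = 400 gives p0 = 0.9656 and p1 = 0.9856. Check: 1.645 × 0.1823 + 0.842 × 0.1191 = 0.2998 + 0.1003 = 0.4000, and (0.4000/0.02)² = 400. So the stated figure is attainable, at BIS P30 = 96.6%.

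The p0 that gives n = 400 under other forms:

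| Form | BIS P30 needed |
|---|---|
| Variance at p1 only | 95.3% |
| Arcsine | 96.3% |
| Score | 96.6% |
| 2% read as relative | 96.8% |
| Continuity correction | 96.9% |
| Two-sided | 97.2% |
| Variance at p0 only | 97.3% |

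The other algebraic solution, a P30 near 2%, has no practical meaning.

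**Step 2. The same test at other BIS P30 values.** Power with 400 is Φ[(0.02·√400 − 1.645·√(p0(1−p0))) / √(p1(1−p1))]. At p0 = 0.90 this is Φ[(0.4 − 0.4935)/0.2713] = Φ(−0.344) = 37%.

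| Assumed BIS P30 | n for 2 points | Power with 400 | Gain detectable with 400 |
|---|---|---|---|
| 95% | 630 | 60% | 2.5 points |
| 90% | 1302 | 37% | 3.5 points |
| 85% | 1894 | 29% | 4.2 points |
| 80% | 2407 | 25% | 4.8 points |

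The form matters near the top: with the variance at p1 only, p0 = 95% needs n = 450 and power with 400 is 76%. It does not rescue the lower values: at 90% that form still needs 1138. Exact binomial power at 90% is 33%.

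**Step 3. Paired reading.** For a one-sided McNemar test,

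n = [1.645·√ψ + 0.842·√(ψ − d²)]² / d²

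A net gain of 2 points requires ψ of at least 2%. For n = 400, ψ = 0.026: 1.645 × 0.1612 + 0.842 × 0.1600 = 0.2652 + 0.1347 = 0.3999, and (0.3999/0.02)² ≈ 400.

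| Assumed discordance | n for 2 points | Power with 400 | Gain detectable with 400 |
|---|---|---|---|
| 2% (minimum) | 307 | 88% | – |
| 2.6% | 400 | 80% | 2.0 points |
| 4% | 616 | 64% | 2.5 points |
| 5% | 771 | 56% | 2.8 points |
| 10% | 1544 | 35% | 3.9 points |

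**Step 4. Link the two readings.** A high BIS P30 does not by itself settle the paired case. At 97% versus 99%, discordance can lie anywhere from 2% to 4% (3% + 1%), so the paired sample size runs from 307 to 616.

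**The case against.** The stated figures contain no arithmetic contradiction. They fit together at a BIS P30 of about 95–97%, and no figure in the article excludes that. A journal article may leave the assumed reference value to the full protocol. A small target difference with a one-sample test is even what planners might write if they had assumed a high published value. All of this stands, and the missing value alone would be no finding. What remains is that the article makes a quantified claim without the condition on which it depends.

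Three stronger readings are tempting, and the documents do not support them:

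- **That the design fails at any ordinary BIS accuracy.** The article gives no P30 for any equation, so there is no documented ordinary value. The Background remark that "those formulae have a certain degree of inaccuracy when used in older people" concerns creatinine-based equations in general, and Laboratory parameters and biomarkers sets BIS1 apart as developed in people over 70. A P30 near 97% fits awkwardly with the study's rationale, but it is not contradicted.
- **That the p-value will be wrong.** The words "considering a 1-sample and 1-sided test" describe the sample-size calculation. The article does not say that the final analysis will test against a fixed BIS value.
- **That one-sample can only mean a fixed reference.** A paired comparison is also a one-sample test on within-person differences. If that was meant, the criticism of the fixed constant falls away, but the condition becomes discordance of at most about 2.6%, which is just as narrow and equally unstated.

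That both equations will be scored on the same people is an inference from where mGFR and creatinine are measured. It is a strong one, but the article does not say so outright.

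**Conclusion.** The point holds in a conditional form. The claim that 400 participants detect a 2-point P30 difference with 80% power is true only near a boundary: BIS P30 of about 95–97% on the one-sample reading, or discordance of about 2.6% or less on the paired reading. Away from it, power falls quickly, for example to 37% at a BIS P30 of 90% or to 56% at 5% discordance. These values are assumptions chosen to show the range; none comes from the documents.

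A sample-size calculation against a fixed BIS P30 leaves out both the sampling error of BIS and the pairing. This should be fixed, but it is not a fatal flaw. It concerns a sub-study, and the main cohort's endpoints (eGFR decline and ESRD) have their own sample-size statement in Data management and statistics.

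**What to change.** - Base both the sample-size statement and the primary P30 comparison on a paired method: McNemar's test or a paired bootstrap confidence interval for the difference in P30.
- Give the assumed BIS P30 and the assumed discordance between the equations, with their source.
- Restate what 400 participants detect with 80% power at one-sided 0.05. As an illustration, this is about 2.5, 2.8 and 3.9 points at 4%, 5% and 10% discordance, all three being assumptions for the sponsor to replace.
- If the 2-point figure is kept, state beside it the BIS P30 or discordance on which it depends.

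The cost is rewording and, in most scenarios, a less favourable stated detectable difference. No extra participants or procedures are needed.
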